## Abstract

**Background:**

Pulp necrosis is one of the main complications of dental trauma. When it happens on an immature tooth, pulp necrosis implies a lack of root maturation and apical closure. A therapy called apexification is required to induce the formation of a calcified apical barrier allowing a permanent and hermetic root filling. The aim of this prospective randomized clinical trial is to compare Mineral Trioxide Aggregate(MTA)with Calcium Hydroxide(CH)as materials used to induce root-end closure in necrotic permanent immature incisors.

**Methods/Design:**

This study, promoted by AP-HP, was approved by the ethics committee(CPP Paris Ile de France IV). 34 children aged from 6 to 18 years and presenting a non-vital permanent incisor are selected. Prior to treatment, an appropriate written consent has to be obtained from both parents and from children. Patients are then randomly assigned to either the MTA(experimental)or CH(control)groups. Recalls are performed after 3, 6 and 12 months to determine the presence or absence of a calcified apical barrier through the use of clinical and radiographic exams. Additional criteria such as clinical symptoms, apical radiolucencies, periapical index(PAI)are also noted.

**Trial registration:**

ClinicalTrials.gov no. NCT00472173 (First inclusion: May 10, 2007; Last inclusion: April 23, 2009; study completed: April 15, 2010)

## Background

Dental injuries are very common in children between six and nine years old. A serious complication of these traumas is the pulp necrosis whose prevalence varies with the type of traumatism from 1-6% for crown fractures to nearly 100% for intrusions [1]. The pulp necrosis of permanent immature teeth implies the interruption of the root formation and apical closure. It is then necessary to implement a therapy, called apexification to induce a hard calcific barrier at the apical end of the root, to achieve the definitive root canal filling. For a long time, calcium hydroxide was the only material used in the apexification procedure: The treatment consists in repeated stimulations with calcium hydroxide, over a six to eighteen months' period, until the apical closure is achieved [2]. Many studies in the literature report inconveniences linked to that procedure:

- The treatment involves numerous visits over a prolonged period and the patients may therefore fail to attend their appointments. It may also lead to a loss of temporary dressings and a re-infection of teeth. It is moreover impossible to perform a permanent restoration [3].

- In retrospective studies, cervical root fractures were said to occur on teeth during or following treatment with calcium hydroxide due to thin dentinal walls in immature teeth as well as to weakened dental structure induced by calcium hydroxide [4-7].

To avoid these inconveniences, the use of new materials potentially inducing mineralisation such as Mineral Trioxyde Aggregate(MTA)was suggested [8]. A review of the existing literature was done to determine if MTA could be considered an alternative to calcium hydroxide in apexification of permanent immature teeth. The analysis of in vitro and animal studies reveals different properties of MTA which seem interesting as regards apexification, offering good sealing ability [9-15], antimicrobial properties [11,16,17], a setting ability uninhibited by blood or water [11,18], biocompatibility, low cytotoxicity [19-22], non-resorbable nature [11,23] and also an effect on the induction of odontoblasts and of a hard barrier [11,24-30]. The MTA(Proroot^® ^MTA, Dentsply Maillefer France)is a medical device benefiting of EC marking. It is a powder mixed with sterile water to obtain a dental filling cement, used routinely for different clinical protocols in odontology. All clinical cases reported in the literature show, after a period of about six to twelve months, an absence of pathological clinical signs, the healing of a possible periapical lesion and the development of an apical closure [31-40]. However, the absence of a clinical comparative prospective study is to be deplored and we do not have the benefit of hindsight. That is why the implementation of a randomized clinical study in a public hospital is interesting to compare calcium hydroxide and MTA in the treatment of non vital immature teeth.

## Methods/Study design

### Objectives

- The main objective of this study is to test the ability of MTA, used as a root-end filling material, to induce a hard calcific barrier to seal hermetically non vital immature anterior permanent teeth with open apices over a 6 month's period.

MTA is a filling material allowing the creation of an artificial apical barrier-the MTA apical plug-but it is not good enough. The advantage of MTA is to induce a very close formation of mineralized tissue which is going to coat gradually the entire apex adhering to the MTA and the root walls. The interest of MTA is not only to create an immediate apical sealing(mechanical barrier)to induce a successful healing but also to promote the root-end growth or apexification, and finally the "bio-integration" of the non-vital immature permanent tooth.

- Secondary objectives:

• To assess the presence or absence of periapical radioluciency indicating the emergence or persistence of an apical periodontitis

• To compare the time required to obtain the clinical healing and the disappearance of clinical symptoms with the two materials: MTA and Calcium Hydroxide, when symptoms such as pain, swelling, sinus tract, abscess or abnormal mobility are present at the beginning of the study.

### Hypothesis

In children with pulp necrosis of a permanent immature incisor, MTA is not better than calcium hydroxide in the rates of a calcified apical barrier, but MTA is more valuable to achieve a biologic periapical barrier before 6 months.

### Research type

Randomized controlled trial(RCT), monocentric, open-labeled, superiority trial

### Subjects

The studied sample is composed of 34 children and teenagers, aged from 6 to 18 years presenting a pulp necrosis of a permanent immature incisor. The root maturation is normally completed 3 or 4 years after the tooth eruption, that is to say around the age of 9 or 10 years as far as incisors are concerned. However some teenagers present teeth damaged by a trauma before their maturation was achieved. That is the reason why such patients are included in the study when those traumas were not or unsuccessfully dealt with. The number of patients needed for this study was calculated prior to investigation with the hypothesis of a higher successful apexification rate in the MTA group compared to the control CH group. The anticipated success rates at 6 months were 5% in the CH group and 50% in the MTA group; Given these hypotheses, it was necessary to include 15 patients in each group that is to say a total of 30 patients to have a 80% statistical power(with a α risk of 5%), to compare the proportion of apical closure at 6 months with a Chi-2 test(two sided). Taking into account an anticipated dropout of 5%, it was decided to include 34 patients. Sample size calculations were computed with nQuery Advisor^® ^6.01. For ethical reasons, the sample size was limited while remaining compatible with the ability to obtain a significant difference between the two materials. The case reports published in the literature show a periapical repair within the first 6 months whereas the apical bridging induced with calcium hydroxide is more often obtained after a period of 6 to 18 months. That is why we hypothesized that after a period of 6 months, at least half of the MTA cases would be a success for the main objective as opposed to a minimal percentage for the calcium hydroxide group.

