### Randomization

Participants are assigned in a treatment group by an independent statistician. Random numbers were randomly determined via a block randomization with a 1:1 ratio and blocks size of 4. The block size was concealed from all researchers. The randomization of the trial is centralized and conducted by an external authority: the Unity of Clinical Research(UCR). After the informed consent form is obtained, the investigator sends a randomization request fax to the UCR that sends back the random number according to the random sequence list. The latter fax is also sent to the hospital pharmacy that delivers the products necessary to the study.

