### Statistical analysis

All the analyses followed an intention-to-treat principle and will be conducted to compare the efficacy of MTA with CH to induce root-end closure in necrotic permanent immature incisors at 6 months. Secondary efficacy endpoints are apical radiolucencies and PeriApical Index(PAI = 1, 2: healthy or PAI = 3, 4, 5: pathological)

Primary endpoints, ie, proportions of patients with an apical barrier close at 6 months will be compared between treatment groups with the Fisher's exact test, such as with the secondary endpoints.

To handle missing data on the primary endpoint, several procedures will be used where the missing values will be either dropped-out or replaced according to 3 simple imputation methods as follows:

- Observed data: patients with missing values are dropped out.

- Worst-case analysis: missing values are considered as a failure(apical barrier not closed at 6 months)in MTA group and as a success in CH group.

- Best-case analysis: missing values are considered as a success(apical barrier closed at 6 months)in MTA group and as a failure in CH group.

- Last Observation Carried Forward(LOCF):previous diagnostic is used to replace missing values.

The assessment of concordance between the two independent investigators about the closure of apical barrier at baseline, months 3, months 6 and months 12 will be given with the Kappa coefficient and the 95% confidence interval.

Analyses will be performed by two statisticians of Biostatistics and Epidemiology unit of Cochin Hospital(Paris)using SAS 9.1(SAS Institute Inc, Cary, North Carolina); tests will be 2-sided, and 0.05 will be used as the threshold for statistical significance.

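### The 15 patients per group give 80% power for a chi-square test, but the primary endpoint is tested with Fisher's exact test, for which 15 per group give about 74%; the 34 enrolled largely close the gap

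*Protocol article*

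**What the plan says.** The Subjects section gives the planning rates: "The anticipated success rates at 6 months were 5% in the CH group and 50% in the MTA group". From these it concludes that "it was necessary to include 15 patients in each group that is to say a total of 30 patients to have a 80" per cent power (in full, "80% statistical power(with a α risk of 5"%), and names the test: "to compare the proportion of apical closure at 6 months with a Chi-2 test(two sided"). It then sets enrolment: "Taking into account an anticipated dropout of 5%, it was decided to include 34 patients".

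The Statistical analysis section says that the primary endpoint, the proportion with a closed apical barrier at 6 months, "will be compared between treatment groups with the Fisher's exact test, such as with the secondary endpoints". Tests there are two-sided at 0.05.

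The Randomization section specifies "block randomization with a 1:1 ratio and blocks size of 4".

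**The concern.** Endpoint, time point, sidedness and significance level agree between the two sections. Only the test differs. In a trial of this size that matters: with 5% expected in the calcium hydroxide (CH) group, 15 patients yield 15 × 0.05 = 0.75 expected successes, and Fisher's test is then very conservative. Its largest true type I error is 1.8% at 15 per group and 2.4% at 17, against a nominal 5%. The price is power.

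The statement carries weight because the Subjects section says the sample was kept small on ethical grounds while still being able to show a difference. That argument rests on the power quoted. A second, smaller discrepancy sits beside it: the step from 30 to 34 patients does not follow from a 5% dropout.

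**Working it through.** **Inputs.** CH 5%, Mineral Trioxide Aggregate (MTA) 50%, power 80%, two-sided alpha 5%, 15 per group, 5% dropout and 34 enrolled (all Subjects); 1:1 allocation (Randomization); two-sided Fisher's exact test at 0.05 (Statistical analysis).

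**1. Reproducing the 15.** The uncorrected chi-square formula with pooled variance under the null is

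n = [z₀.₉₇₅ √(2p̄(1−p̄)) + z₀.₈₀ √(p₁(1−p₁) + p₂(1−p₂))]² / (p₂−p₁)², with p̄ = (0.05 + 0.50)/2 = 0.275.

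- First term: 1.960 × √(2 × 0.275 × 0.725) = 1.238
- Second term: 0.842 × √(0.0475 + 0.25) = 0.459
- n = (1.238 + 0.459)² / 0.45² = 14.2, rounded up to 15

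The stated figure reproduces exactly. The continuity-corrected formula gives 18.4, so 19. The 15 therefore comes from the uncorrected chi-square test. At 15 per group, power for that test is 82.3% by the approximation and 87.0% by exact enumeration.

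**2. Power of the planned test.** For each possible pair of success counts (x in MTA, y in CH), compute the two-sided Fisher p-value. Then add Bin(x; n_MTA, 0.50) × Bin(y; n_CH, 0.05) over all pairs with p ≤ 0.05.

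| Evaluable MTA/CH | Total | Fisher power |
|---|---|---|
| 17/17 | 34 | 81.3% |
| 16/17 | 33 | 86.1% |
| 17/16 | 33 | 82.4% |
| 16/16 | 32 | 77.7% |
| 15/17 | 32 | 85.2% |
| 17/15 | 32 | 83.5% |
| 15/15 | 30 | 73.6% |
| 14/16 | 30 | 81.6% |
| 16/14 | 30 | 80.2% |
| 13/17 | 30 | 78.9% |
| 17/13 | 30 | 75.6% |

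Power does not rise smoothly with the total, because the test is discrete and equal arms are its worst case. With equal arms, 17 per group is the smallest size reaching 80%.

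**3. Power at the enrolled 34 with loss.** Start from 17 per group and let losses fall at random.

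- Two lost (2/34 = 5.9%): the split is 16/16 with probability 17 × 17/561 = 0.515, and 15/17 or 17/15 with probability 136/561 = 0.242 each. Average: 0.515 × 77.7% + 0.242 × (85.2% + 83.5%) = 80.9%.
- Independent 5% loss per patient, averaged over all resulting splits: 81.8%.
- Four lost (11.8%): the probabilities are 0.399 for 15/15, 0.249 each for 14/16 and 16/14, and 0.051 each for 13/17 and 17/13. Average: 0.399 × 73.6% + 0.249 × (81.6% + 80.2%) + 0.051 × (78.9% + 75.6%) = about 78%.

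**4. Dropout step.** 30/0.95 = 31.6, so 32. Conversely, (34 − 30)/34 = 11.8%. Rounding to whole blocks of 4 would give 32 or 36, so it does not explain 34.

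**5. An alternative exact test.** Boschloo's unconditional test has power 84.3%, 81.3% and 85.1% at 15, 16 and 17 per group, with true size of at most 4.3%. The uncorrected chi-square test itself exceeds its nominal level slightly: up to 5.5% at 15 per group and 5.8% at 17.

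**The case against.** The sample size sentence names its own test and is correct for it, so this is an inconsistency between two sections and not a miscalculation. That stands.

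A reader might infer that the trial has only 74% power. The documents do not support this. They enrol 34, and 73.6% needs four losses, more than twice the anticipated rate, that also leave exactly 15/15; even at 30 evaluable, a 14/16 or 16/14 split keeps power just above 80%.

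A reader might also infer that the target is missed at the planned dropout, because 16/16 gives 77.7%, and that 34/0.95, or 36 patients, should be enrolled. That looks at one split only. Averaged over the ways in which two patients can be lost, power is 80.9%.

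The protocol does not claim that 34 equals 30/0.95, and the two patients beyond 32 err on the safe side. This also stands, although the sentence still gives 5% as the reason for 34.

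Finally, Fisher's test is a standard and valid choice with so few expected events. It protects the type I error and introduces no bias. Boschloo's test is an option, not the correction of an error.

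**Conclusion.** The concern holds in limited form. For the planned test, 15 evaluable patients per group give 73.6% power, not 80%, so the requirement stated in the Subjects section is wrong for the analysis that will be run. The 34 enrolled roughly restore the target: 81.3% with complete data and 81 to 82% on average at 5% loss.

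Much of the margin presented as dropout cover therefore pays for the change of test. With equal arms it takes all four patients. Averaged over uneven splits, 32 evaluable suffice and 30 do not.

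These figures assume true rates of 5% and 50%, losses unrelated to arm or outcome, analysis of observed cases, and 17 randomised per group. Since 34 is not a multiple of 4, the last block is incomplete and 18/16 is possible. The same enumeration gives 86.3% for 18 MTA/16 CH and 85.2% for 16 MTA/18 CH, so this does not weaken the conclusion.

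The issue is moderate. It affects the justification of the sample size, and leaves the endpoint, the effect estimate and the control of type I error untouched.

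**What to change.** Name the same test in the Subjects and Statistical analysis sections.

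- **If Fisher's test is kept:** state that its power at 5% versus 50% is about 74% with 15 evaluable per group and about 81% at the enrolled 34, with or without the anticipated 5% loss.
- **Dropout sentence:** say that 5% loss from 30 would require 32, and that 34 allows about 12% loss down to 30.
- **Option, only if no outcome data by group have been seen:** prespecify Boschloo's exact unconditional test for the primary endpoint, with about 84% power at 15 per group and size below 5%. The article reports the study as completed in April 2010, so this condition has to be checked first; if it fails, keep Fisher's test.

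Moving the analysis to the uncorrected chi-square test would also align the sections, but that test slightly exceeds 5% here.

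The cost is wording in two sections, and a less favourable power figure at 15 per group if Fisher's test stays. Boschloo's test may need software outside the specified SAS 9.1. No extra patients are needed.

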#### Inclusion criteria

I1-Patient presenting a non-vital permanent immature incisor for which an apexification treatment is indicated

I2-Aged 6-18 years

I3-Written informed consent obtained from each parent and from the child

I4-Medical exam

#### Exclusion criteria

E1-General pathology

E1.1-History of uncontrolled diabetes

E1.2-Immunosuppression

E1.3-Severe asthma

E1.4-Chronic systemic disease if a treatment is required

E1.5-Eating disorder(anorexia, bulimia, malnutrition, ...)

*E2-Oral pathology: *Periodontal disease

E3-Corticosteroid treatment during the last 3 months

E4-Non-affiliation to a social security scheme

#### Suspension criteria

S1-Poor compliance

S2-New trauma or new complication

S3-Intercurrent illness requiring discontinuation of the trial

When patients are lost sight of, observations must be noted down in the CRF until the last effected visit. The investigators will do their best to contact the patient and find out why the patient ceased being in the trial.

### Randomization

Participants are assigned in a treatment group by an independent statistician. Random numbers were randomly determined via a block randomization with a 1:1 ratio and blocks size of 4. The block size was concealed from all researchers. The randomization of the trial is centralized and conducted by an external authority: the Unity of Clinical Research(UCR). After the informed consent form is obtained, the investigator sends a randomization request fax to the UCR that sends back the random number according to the random sequence list. The latter fax is also sent to the hospital pharmacy that delivers the products necessary to the study.

### Design of the study-Interventions

For each patient the protocol is composed of 7 sessions(Table 1). The follow-up takes place over a 12 months' period. Day 0 is considered as the day of the first treatment session.

**Table 1 T1:** Study protocol for each included patient

Sessions	1	2	3	4	5	6	7
**Timing**	D-15 to D0	D0	D + 15	D+21	3 months	6 months	12 months

**Written informed consent**	X						

**Inclusion and exclusion criteria**	X						

**Diagnosis of immature tooth pulp necrosis**	X						

**Clinical exam: symptoms**	X	X	X	X	X	X	X

**Radiographic exam**	X	X	X	X	X	X	X

**Calcium hydroxide filling or renewal**		X	X(CH group)		X(CH group-no barrier)	X(CH group-no barrier)	

**Apical filling with MTA**			X(MTA group)				

**Complete filling with gutta-percha**				X(MTA group)	X(CH group and apical barrier)	X(CH group and apical barrier)	

1. Day 0-14/Day 0: Inclusion and selection visit

Diagnosis of pulp necrosis, clinical and radiographic exams

Written informed consent is obtained from both parents and from the child.

2. Day 0: Calcium hydroxide canal conditioning regardless of the treatment group

This treatment is performed under local anesthesia with Articaïne with adrenalin 1/200000(Septanest, Septodont, France), after placement of a rubber dam. After preparing an access cavity and establishing the working length by taking a radiograph with a file inserted into the root canal within 1 mm of the radiographic apex, the canal is cleaned by irrigation with 3% sodium hypochlorite(Parcan, Septodont, France)and the use of manual files. The cleaning and shaping are realized with files with a very light parietal action to avoid the canal widening and the weakening of the root walls. Above all, it consists in removing the pulp remnants. The most important thing is to observe the vacuity and cleanliness of the canal using operative microscopy. Considering the root immaturity, it is actually a cleaning and desinfection without shaping. Then the canal is dried with paper point and can be filled with calcium hydroxide. Calcium hydroxide paste is prepared by mixing the calcium hydroxide powder(obtained from the hospital pharmacy)with an anaesthetic solution(Scandicaïne, Septodont, Saint Maur des Fossés, France). A plug of calcium hydroxide is deposed in the canal and condensed to the apical end of the root with a plugger. Other applications of calcium hydroxide are realized, until complete canal filling. The excess moisture is dried between each input with sterile paper points. The intracanal dressing quality is checked with a radiograph. The access cavity is temporarily sealed with a resin modified glass ionomer cement(Fuji II LC, GC, Bonneuil sur Marne, France). This calcium hydroxide canal conditioning is performed for all patients to allow the complete disinfection already obtained thanks to irrigation with sodium hypochlorite and the use of manual files, to control acute symptoms and to allow further treatments.

3. Day0+15: MTA apical filling for the testing group/calcium hydroxide renewal for the control group

This session starts with a local anesthesia, the placement of a rubber dam and the removal of all the calcium hydroxide. For this procedure, the canal has to be cleaned by irrigation and the use of ultrasonic files to remove all the calcium hydroxide. The use of EDTA allows a more complete elimination but due to these teeth immaturity the EDTA is not recommended. Then, the treatment differs among the treatment group:

For the MTA group, a MTA plug is placed into the canal with a root canal messing gun and condensed to the apical end of the root with a plugger to create a 4 mm apical plug of MTA. The pipe of the MTA gun is adjusted for the piston to deliver a 3 mm plug. Coarse paper points are used upside down to perfect the MTA adaptation to the apical walls. A radiographic control allows the practitioner to verify the good placement of MTA. A paper point moistened with sterile water is placed in the canal to produce an ambient humidity for the MTA to achieve its solidification. The access cavity is filled with conventional glass ionomer cement(Fuji IX, GC, Bonneuil sur Marne, France).

- For the CH group, the complete filling with calcium hydroxide is obtained as the first treatment session.

4. Day 0+21: Control for the CH group/complete filling with gutta-percha for the MTA group. The hardness of the MTA is checked with an endodontic file and the root canal filling with gutta-percha can be realized in contact with MTA. This filling is realized with the Schilder's technique: warm gutta-percha compacted with the Touch'n Heat(SybronEndo, Henry Schein, Alfortville, France). The access cavity is then sealed with a composite resin.

5. 3 months: clinical and radiographic control for all patients, and calcium hydroxide renewal for CH group patients.

6. 6 months: clinical and radiographic control for all patients and for CH group patients, calcium hydroxide renewal or complete root filling with gutta-percha if an apical barrier is present.

7. 12 months: clinical and radiographic control

For the teeth of CH group not filled with gutta-percha, the following treatment is realized outside study.

All the treatment sessions are realized in the same dental office, under local anesthesia, after placement of a rubber dam and with optical aids, by the same two operators, one assistant and the other alternately.

The X-Rays of each patient are standardized so that they can be compared. When each patient has his first X-Ray taken, the patient is asked to bite into a piece of silicone which enables the operator to put the film holder in the same position at each session(Figure 1a, b, c). Thus the radiographs can be reproducible.(Figures 2a, b, c)

